# The Impact of Normal Saline or Balanced Crystalloid on Plasma Chloride Concentration and Acute Kidney Injury in Patients With Predicted Severe Acute Pancreatitis: Protocol of a Phase II, Multicenter, Stepped-Wedge, Cluster-Randomized, Controlled Trial

**DOI:** 10.3389/fmed.2021.731955

**Published:** 2021-10-04

**Keywords:** acute pancreatitis, saline, crystalloid, acute kidney injury, intravenous fluid

## Abstract

**Introduction/aim:** The supraphysiologic chloride concentration of normal saline may contribute to acute kidney injury (AKI). Balanced crystalloids can decrease chloride concentration and AKI in critically ill patients. We aim to test the hypothesis that, in patients with predicted severe acute pancreatitis (pSAP), compared with saline, fluid therapy with balanced crystalloids will decrease plasma chloride concentration.

**Methods/Design:** This is a multicenter, stepped-wedge, cluster-randomized, controlled trial. All eligible patients presenting to the 11 participating sites across China during the study period will be recruited. All sites will use saline for the first month and sequentially change to balanced crystalloids at the pre-determined and randomly allocated time point. The primary endpoint is the plasma chloride concentration on day 3 of enrollment. Secondary endpoints will include major adverse kidney events on hospital discharge or day 30 (MAKE 30) and free and alive days to day 30 for intensive care admission, invasive ventilation, vasopressors, and renal replacement therapy. Additional endpoints include daily serum chloride and sequential organ failure assessment (SOFA) score over the first seven days of enrollment.

**Discussion:** This study will provide data to define the impact of normal saline vs. balanced crystalloids on plasma chloride concentration and clinical outcomes in pSAP patients. It will also provide the necessary data to power future large-scale randomized trials relating to fluid therapy.

**Ethics and Dissemination:** This study was approved by the ethics committee of Jinling Hospital, Nanjing University (2020NZKY-015-01) and all the participating sites. The results of this trial will be disseminated in peer-reviewed journals and at scientific conferences.

**Trial registration:** The trial has been registered at the Chinese Clinical Trials Registry (ChiCTR2100044432).

## Introduction

The most important determinant of mortality in patients with acute pancreatitis (AP) is organ failure (1). Renal failure or acute kidney injury (AKI) occurs in 25–59% of patients with severe AP (2, 3). It may be due to several factors, including hypovolemia, hypoxemia, pancreatic proteolytic enzymes, impairment of renal microcirculation, decreased renal perfusion pressure, tissue edema, and/or intrabdominal hypertension (4–6). Maintaining normovolaemia by timely and adequate fluid therapy to preserve organ perfusion is considered the cornerstone of the management of AP in the acute phase (7–9).

Normal saline (NS or 0.9% sodium chloride) is the most frequently used isotonic crystalloid fluid for resuscitation in the acute setting around the world (10). Because the chloride concentration of NS (154 mmol per liter) is significantly higher than plasma chloride concentration (94–111 mmol per liter), there is a risk of hyperchloremic metabolic acidosis. The risk of this increases with systemic inflammation and impaired renal perfusion through multiple mechanisms (11). However, the clinical impact of the increased chloride load with NS resuscitation is not fully understood. There is some evidence that it increases the risk of AKI and the need for renal replacement therapy (RRT) in critically ill patients (12, 13), but there is no reliable data in AP patients.

Balanced crystalloid fluids are an alternative to NS, and some current guidelines recommend Lactated Ringers (LR) for early resuscitation, but there is a lack of high-quality evidence (7, 8, 14). Previous studies showed that LR resuscitation can decrease inflammatory markers but did not improve clinical outcomes in patients with predominantly mild AP (15–17). These studies did not report changes in plasma chloride or the incidence of AKI. Our previous study showed that aggressive resuscitation and increased chloride load during the first 24 hours were risk factors for new-onset AKI in patients with moderately severe and severe AP (18). This study aims to compare the impact of NS and a balanced crystalloid fluid on the plasma chloride concentration and the incidence of AKI in patients with predicted severe AP (pSAP).

## Methods and Analysis

### Aim and Objectives

The primary objective of the CLEVER-AP trial is to determine whether, compared to NS, balanced crystalloids significantly reduce plasma chloride concentration in patients with pSAP. The secondary objective is to determine whether a lower plasma chloride concentration is associated with reduced renal dysfunction and improved clinical outcomes.

### Study Design

The present study is an investigator-initiated, stepped-wedge, cluster-randomized trial, in which each participating hospital will begin in the control phase (patients receiving NS) and transition to the intervention phase (patients receiving balanced crystalloids) at randomly assigned time points (wedge). This trial was registered at the Chinese Clinical Trials Registry (ChiCTR2100044432).

### Trial Committees

A Trial Management Committee (TMC) was formed comprising the primary investigators, supported by all the other co-investigators (clinical and non-clinical) from the participating sites and members of the Chinese Acute Pancreatitis Clinical Trials Group (CAPCTG) coordinating center. The TMC is responsible for the day-to-day running and management of the trial. An expert clinical panel consisting of experts from the CAPCTG was organized to provide governance and audit the study (some are not from the participating sites). This panel will also assist with crucial clinical decision-making, such as the introduction of RRT.

A writing and publication committee is responsible for drafting the manuscript and submission of the manuscript to proper academic journals. It will also decide on the authorship of this study.

### Study Population

All adult patients with AP admitted to the participating sites will be assessed for eligibility after admission. This trial will include all patients from the 11 hospitals who met the eligibility criteria during the enrollment period.

### Eligibility Criteria

The inclusion and exclusion criteria are as follows:

#### Inclusion Criteria

Diagnosis of acute pancreatitis (19): symptoms and signs of acute pancreatitis based on abdominal pain, serum amylase at least three times the upper limit of the normal range, and/or characteristic findings on computed tomography;Predicted severe acute pancreatitis, based on APACHE-II score≥8 and CRP>150 mg/L.Recruitment within 72 h from the onset of the symptoms;Age between 18 to 70 yrs old;

#### Exclusion Criteria

Patients with chronic renal disease [All patients with an eGFR<60 ml/min/1.73 m^2^ for three months are defined as having chronic kidney disease (20)].Patients who need emergent RRT at the time of admission. The indication for RRT will be according to the criteria described by Bellomo et al. (21).Patients who are pregnant or lactating at the time of enrollment.Patients who undergo RRT before admission.Patients receiving percutaneous or transmural drainage for pancreatic necrotic collections or surgery before admission or requiring emergency surgery due to abdominal compartment syndrome, bowel ischemia, etc., at admission.Patients present with fulminant multiple organ failure with predicted death within 24–48 hrs (e.g., severe respiratory failure, severe systemic circulatory failure, coma, or other dangerous symptoms that are difficult to reverse).Patients with a known history of severe cardiovascular, respiratory, renal, hepatic, hematologic, or immunologic disease defined as (1) greater than New York Heart Association class II heart failure, (2) active myocardial ischemia, or (3) cardiovascular intervention within previous 60 days, (4) history of cirrhosis or (5) severe chronic obstructive pulmonary disease requiring home oxygen.

### Randomization Methods

We used a computer-generated randomization scheme to determine the order in which each participating site crosses over from the control phase to the intervention phase. According to the stepped wedge design, all sites will initiate recruitment using NS for fluid therapy in the first month. Every month thereafter, one hospital will be randomized to use balanced crystalloids without a transition period. The assignment of patients will depend on their admission date (Figure 1).

**Figure 1 F1:**
[figure not shown]
Crystalloid assignment during the trial. All sites will initiate the trial with 0.9% saline (S) as the intravenous fluid at the first month and sequentially change over to balanced crystalloids (B) without a transition period.

This study is open-label. Therefore, no blinding method will be applied to the investigators. However, study participants, operators who perform the blood test, and data analysts will be masked to the allocation sequence. Study investigators will be blinded to the allocation sequence, with only the next hospital randomized for rollout being revealed a week before each transition time point.

### Sample Size, Centers, and Recruitment

According to the previous study, the standard deviation of serum chlorine in patients with severe acute pancreatitis is conservatively estimated at 6mmol/L (22). A total of 240 patients will be recruited from 11 centers within 12 months (20 patients per month). They will provide 90% power to detect the serum chlorine difference of 1.5 mmol/L or more between the balanced crystalloid and the saline group on the basis of within period intra-class correlation coefficient (ICC) of 0.05 and cluster auto-correlation (CAC) of 0.5.

The starting date of patient recruitment was Apr 1^st^, 2021, and the planned finishing date is Mar 31^st^, 2022. The follow-up will be finished after the discharge of the last recruited patient.

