### Statistical Analysis

The reporting and presentation of this trial will follow the CONSORT guidelines for stepped-wedge trials (24). Based on the principle of intention to treat (ITT), a full-analysis set (FAS) will be performed on the population with outcome reporting (day3 chloride concentration). FAS will be used for the analysis of baseline characteristics and main therapeutic interventions. The safety set (SS) will include all enrolled patients for assessing the safety profile of the intervention.

Descriptive statistics will be used to assess any marked baseline differences in demographics or outcome measures between the two groups, taking clustering into account. Comparisons of binary outcomes will be expressed as relative risk with 95% confidence intervals and comparisons of continuous outcomes as mean differences together with 95% confidence intervals. Between-group comparisons will be made using generalized linear mixed-model (GLMMs) with a hospital-level random effect to address clustering by hospital and random slopes of time to account for temporal effects, as delineated by Hussey and Hughes. Two-sided 5% significance levels will be used to identify statistically significant results. All confidence intervals reported will be 95% confidence intervals.

A series of subgroup analyses will be conducted for the evaluation of the primary endpoint: age (dichotomized at 60 years old), referral or non-referral, presence of AKI at enrollment, and presence of organ failure at enrollment.

For any possible missing data, we assume the data is missing at random while performing analyses by GLMM. Moreover, a series of sensitivity analyses after imputing the missing primary outcome using worse-case (i.e., values at baseline), Last Observation Carried Forward (LOCF), and multiply imputation will be used to validate and test the robustness of our trial result.

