## Discussion

The best crystalloid for the early resuscitation of patients with AP remains controversial. The CLEVER-AP trial will, for the first time, provide evidence regarding the effects of normal saline and balanced crystalloid fluid on plasma chloride concentration and AKI in patients with pSAP. The findings of this trial will have direct clinical consequences as it will provide definitive evidence.

MAKE30 is identified as a key clinical endpoint, and it has been used successfully in several fluid trials (12, 25). MAKE30 is the composite of death, new RRT, or persistent renal dysfunction (PRD), which is recommended by the National Institute of Diabetes and Digestive and Kidney Diseases (NIDDK) workgroup for capturing effects of the short-term or longer-term evolution of AKI (26, 27). As such, it is a patient-centered and highly relevant endpoint for clinical research. Adopting MAKE30 as a key secondary endpoint will allow comparison with other major trials conducted with different patient populations.

The stepped-wedge cluster randomized design is adopted for the CLEVER-AP trial based on both methodology and clinical merits it could provide. From the methodology perspective, it uses the hospital as the entity of randomization because this will minimize the risk of treatment contamination and could greatly reflect the real-life practice across each hospital compared to randomization at the patient or physician level. Moreover, this design could model and assess the underlying temporal trends of the intervention with all hospitals accessing the intervention at the end of the rollout period. From the clinical perspective, since massive intravenous fluid infusion is essential and crucial in managing early acute pancreatitis, randomization at the patient level would make the intervention (fluid infusion with different types of crystalloids) vulnerable to misuse, potentially leading to contamination (12, 28). Moreover, the routine consent-and-randomization process in patient-level randomized trials takes a lot of time, during which no one knows what fluid should be used before randomization. Therefore, intravenous fluid before randomization, which could be massive, could significantly confound the trial results.

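### 240 patients give about 28% power for a 1.5 mmol/L chloride difference, not the stated 90%; 90% power is reached only at about 3.5 mmol/L

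*Protocol article*

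**What the plan says.** The section on sample size, centers and recruitment gives the full set of inputs. On variability: "the standard deviation of serum chlorine in patients with severe acute pancreatitis is conservatively estimated at 6mmol/L". On numbers: "A total of 240 patients will be recruited from 11 centers within 12 months (20 patients per month"). On correlation: "within period intra-class correlation coefficient (ICC) of 0.05 and cluster auto-correlation (CAC) of 0.5". From these it concludes: "They will provide 90% power to detect the serum chlorine difference of 1.5 mmol/L or more between the balanced crystalloid and the saline group".

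The layout is in the section on randomization methods. All hospitals use saline in month 1, and then: "Every month thereafter, one hospital will be randomized to use balanced crystalloids without a transition period". The statistical analysis section sets the test level, "Two-sided 5% significance levels will be used to identify statistically significant results", and a mixed model with a hospital random effect and an allowance for time. The primary endpoint is one day-3 value per patient, and each month brings new patients, so the design is cross-sectional.

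**The concern.** The stated power cannot be obtained from the stated inputs. A difference of 1.5 against a standard deviation of 6 is a standardised effect of 0.25, and 240 patients are too few for that even in the most efficient two-arm design. A stepped wedge adjusted for time is less efficient still, because treatment is partly confounded with calendar month.

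This is the only power justification in the document, and it concerns the primary endpoint. It implies a 10% risk of missing a true difference of 1.5 mmol/L; the risk on the plan's own inputs is about 72%. A non-significant result could then be read as evidence against a 1.5 mmol/L effect, which the design cannot provide. The abstract also says that the trial will supply data for powering later trials, so an uncorrected figure could mislead that planning.

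**Working it through.** **Inputs (all from the protocol article)**
- Total SD 6 mmol/L, difference 1.5 mmol/L, ICC 0.05, CAC 0.5, 240 patients, 11 hospitals, 12 months (sample size section).
- One hospital crosses per month after an all-saline first month (randomization section): 11 × 12 = 132 hospital-months, of which 11 + 10 + … + 1 = 66 are on saline and 66 on balanced crystalloid.
- Two-sided 5% (statistical analysis section).
- Patients per hospital-month: m = 240/132 = 1.82. The 20 patients per month are the total over all sites, since 20 × 12 = 240.

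**Step 1. Benchmark without stepped-wedge theory.** Take 120 against 120, individually randomised, with no clustering:
- SE = 6 × √(2/120) = 0.775.
- Power = Φ(1.5/0.775 − 1.96) = Φ(−0.02) = 49%.
- For 90% power, n per arm = 2 × (1.960 + 1.2816)² × 36/1.5² = 336.2, so 337 per arm or 674 in total.

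**Step 2. The planned design.** The variance of the treatment effect comes from generalised least squares on hospital-month means, with 12 fixed period effects and these components:
- hospital: 36 × 0.05 × 0.5 = 0.9
- hospital-by-month: 36 × 0.05 × 0.5 = 0.9
- residual: 36 × 0.95/1.82 = 18.8

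Results:
- SE = 1.085 mmol/L.
- Power for 1.5 mmol/L = Φ(1.5/1.085 − 1.96) = Φ(−0.577) = 28.2%. With a t distribution on 9 df it is 23.5%.
- Detectable at 90% power: 3.2415 × 1.085 = 3.52 mmol/L.
- Detectable at 80% power: 2.8016 × 1.085 = 3.04 mmol/L.
- Half-width of the 95% confidence interval: 1.96 × 1.085 = 2.1 mmol/L.

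**Step 3. Attempts to reach 90%**

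| Variant | Power for 1.5 mmol/L |
|---|---|
| Plan's inputs, categorical time | 28.2% |
| Linear time | 28.2% |
| CAC = 1 | 26.9% |
| Correlation decaying over months | 29.2% |
| Random time slope (assumed variance 0.01 to 0.05) | 27% to 25% |
| ICC 0 to 0.10, CAC 0.5 to 1.0 | 26% to 33% |
| m rounded up to 2 | 30.1% |
| One-sided 5% | 39.7% |
| No adjustment for time | 45.3% |
| One hospital supplies 40% of patients (assumed) | 24% to 26% |
| 20 patients per hospital per month (N = 2,640) | 91.0% |

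The first ten rows, which keep 240 patients or (with m rounded up) 264, stay below 50%. In the last row the SE is 0.455 and 1.5/0.455 − 1.96 = 1.34. Solving for m at exactly 90% gives 18.9 patients per hospital-month, about 2,490 in total.

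One other input slip also lands near 90%: using 6 as the variance instead of the SD gives 92.3%.

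**The case against.** - **Baseline adjustment could reduce the variance.** It could, but the calculation is stated for an SD of 6 mmol/L and the article gives no correlation with baseline chloride. In this design the SD would have to fall to about 2.6 mmol/L for 90% power.
- **The time model is not fully specified.** The sample size section does not say how time enters, and the analysis section speaks of random slopes of time, whereas step 2 uses fixed monthly effects. That is true, but the choice moves power only between about 25% and 29%.
- **The true effect may exceed 1.5 mmol/L.** The plan does refer to that difference or more, and a true difference of 3.5 mmol/L would be detected with about 90% power. But the claim attaches 90% to 1.5 mmol/L, and there it is false. The planned confidence intervals would show the imprecision, so a misreading is a risk and not a certainty.
- **Limited power is already conceded.** The limitations section concedes it only for patient-centred outcomes such as MAKE 30. It leaves the claim for the primary endpoint standing.
- **The cause is conjecture.** This stands. No document says how the 90% was obtained, and more than one slip comes close to it. The error does not depend on the explanation.
- **The Discussion's claim does not cite the power calculation.** This also stands. "The findings of this trial will have direct clinical consequences as it will provide definitive evidence" covers kidney injury as well as chloride, so changing it is a separate wording matter.

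**Conclusion.** The power statement is wrong as written. Under the plan's own inputs, power for 1.5 mmol/L is about 28% with a normal reference distribution (about 24% with t on 9 df), and 90% power is reached at about 3.5 mmol/L. These figures assume equal recruitment across hospitals and months, fixed monthly effects, one day-3 value per patient and no dropout, for which the article gives no figure. Relaxing the correlation and time assumptions leaves time-adjusted two-sided power between about 25% and 33%. The 49% from the unclustered benchmark shows that 90% is out of reach at 240 patients and an SD of 6 even with no clustering and no adjustment for time. Confidence is high. The correction is needed because the figure is the sole justification of the sample size for the primary endpoint.

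**What to change.** Keep 240 patients and replace the power sentence in the sample size section with text such as:

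> With an SD of 6 mmol/L, a within-period ICC of 0.05, a CAC of 0.5, 11 hospitals, 12 monthly periods and about 1.8 patients per hospital per month (240 in total), the trial has about 28% power at the two-sided 5% level for a difference of 1.5 mmol/L, 80% power for about 3.0 mmol/L and 90% power for about 3.5 mmol/L. A non-significant result does not exclude a difference of 1.5 mmol/L.

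State there that 20 per month is the total over all hospitals, and name the model and software behind the calculation. Extend the limitations section to cover the primary endpoint, and moderate the Discussion's wording on how conclusive the trial will be.

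The cost is a wording amendment and a less favourable stated power. There is no change to enrolment, design or treatment. Reaching 90% power for 1.5 mmol/L in this layout would instead take about 2,490 patients, roughly ten times the planned number.

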### Study Interventions

Study protocol determines only the choice of intravenous isotonic crystalloid: 0.9% sodium chloride or other hyperchloremic solutions (saline group) vs. the Sterofundin ISOTM (balanced crystalloid group). The compositions of each crystalloid solution are given in Additional file 1: Supplementary Table 1.

#### Group 1: Balanced Crystalloid Fluid

Patients will receive Sterofundin ISOTM (B. Braun) whenever isotonic intravenous fluid administration is ordered by the treating clinical team for seven days after enrollment or until discharge or death (whichever happens first).

#### Group 2: NS Fluid

Patients assigned to saline fluid will receive 0.9% Saline or other hyperchloremic solutions whenever isotonic intravenous fluid administration is ordered by the treating clinical team for seven days after enrollment or until discharge or death (whichever happens first).

#### Principles for Fluid Therapy

For patients who are not resuscitated before enrollment, fluid resuscitation will be initiated based on the 2013 IAP/APA guidelines (7). Briefly, 5–10 ml/kg/h of the study crystalloids should be used until resuscitation goals are reached. The resuscitation targets include one or more of the following: (1) non-invasive clinical targets of heart rate <120/min, mean arterial pressure between 65 and 85 mmHg, and urinary output >0.5ml/kg/h, (2) invasive clinical targets of stroke volume variation, and intrathoracic blood volume determination, and (3) biochemical targets of hematocrit 35–44% (7). For patients who are resuscitated before enrollment, the assessment of fluid responsiveness and the rate of crystalloid prescription will be determined by the treating physicians based on the resuscitation goals mentioned above.

